#### Adverse events

At each control visit, adverse events will be routinely screened for by asking a non-leading question to the patient such as: ‘Have you had any health problems since your last visit?’. In case of an emergency, the principal investigator will be contacted. Serious adverse events occurring during the clinical trial must be reported within 24 h to the principal investigator. If the principal investigator is not available, patients are referred to the on-call psychiatrist at the Ghent University Hospital. All participants are insured through a no-fault insurance policy conform Belgian law for human experiments. Insurance information and all contact details are provided in the informed consent document.

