### Procedure

Outcome assessors and/or ECT-physicians will provide adequate verbal and written information regarding the study to all eligible patients at the ECT-clinic. Researchers will obtain written informed consent from all patients willing to participate and able to give consent. After consenting to participate and before the start of ECT treatment, all patients will complete baseline cognitive function assessment (CANTAB, PASAT), cognitive complaints (SSMQ), depressive symptomatology (BDI-II, HAM-D), depressive status (RDQ), rumination (RRS-10) and quality of life (QLDS). After ECT completion, cognitive functioning (CANTAB, PASAT), cognitive complaints (SSMQ), depressive symptomatology (BDI-II, HAM-D), depressive status (RDQ), rumination (RRS-10) and quality of life (QLDS) will be assessed. Moreover, all patients will receive standard clinical care. Patients will receive standard pharmacological relapse prevention, under the responsibility of their treating physician, started during (nortriptyline) or after (lithium) ECT by combining nortriptyline (50-150 ng/ml) and lithium (≥0.5 mmol/l) for MDD and lithium (≥ 0.5 mmol/l) alone for BDD. In case of contra-indication for nortriptyline and/or lithium, alternative relapse prevention options will be explored by the treating physician. As is standard clinical care, monthly lithium dosing and testing of renal and thyroid function will be performed by the treating physician. If renal function deteriorates during follow-up this should be reported as an adverse event and may necessitate lithium discontinuation. Before dismissal from the ward participants will receive a two-session CBT-based relapse prevention group therapy and individual counseling by a social worker. Only patients who achieve a 25% or more reduction in BDI-II or HAM-D scores [36] will be randomly assigned to one of two conditions (CCT or active control), see Fig. 1 as cognitive control training has evidence as a relapse prevention strategy and not as a treatment for MDE. Non-responders to ECT will be excluded to allow further clinical treatment for MDE outside of this study protocol. After completion of the CCT, relapse of depression will be monitored for a period of 6 months using mobile assessments of depression (every 2 weeks) and telephone interviews in case of possible relapse. If there is an indication of relapse, patients will be assessed by the semi-structured Mini International Neuropsychiatric Interview (MINI v7.0.0) depressive episode module (A) and referred for psychiatric assessment to their treating psychiatrist for adequate clinical care if necessary. Patients who relapse will be excluded only if they receive a subsequent ECT-course as this might affect cognitive parameters. At three and 6 months, a more extensive evaluation will be performed investigating cognitive parameters (SSMQ), depressive symptomatology (BDI-II, HAM-D), depressive status (RDQ), rumination (RRS10) and quality of life (QLDS). We refer to Fig. 2 for an overview of the study design and Table 1 for the trial registration data set.

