#### Assessment of depression relapse

Patients will receive a text message once every 2 weeks (except at 3 and 6 months post-ECT; when they are invited for a more thorough interview at the hospital) to enquire whether they experienced either core symptom of depression over the past 2 weeks: 1) Have you been consistently depressed or down, most of the day, nearly every day, for the past 2 weeks?; 2) In the past 2 weeks, have you been much less interested in most things or much less able to enjoy the things you used to enjoy most of the time? . Answer can be yes or no. The text messages will be sent using SurveySignal at 18.00 h containing a link to a two question LimeSurvey questionnaire. If the patient does not respond within the first hour, a reminder text message will be sent. If the patient either does not respond to the screening questions within a 24-h timeframe, or answers either of the questions affirmatively, the patient will be called by the researcher to conduct the semi-structured Mini International Neuropsychiatric Interview (MINI v7.0.0) depressive episode module (A). If a relapse has concluded, patients will be referred for psychiatric assessment to their treating psychiatrist for adequate clinical care. These phone calls will be recorded and stored for later evaluative purposes and diagnosis by an independent rater.

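### Adverse events are actively asked about only at control visits, apparently 9 to 13 weeks apart in follow-up, while the existing fortnightly survey carries no adverse-event item

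*Protocol article*

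**What the plan says.** The Adverse events section sets the method and the recall window. Events are sought as follows: "At each control visit, adverse events will be routinely screened for by asking a non-leading question". The example question is "Have you had any health problems since your last visit". The same section adds a deadline, "Serious adverse events occurring during the clinical trial must be reported within 24 h to the principal investigator", and an emergency route, "In case of an emergency, the principal investigator will be contacted", with an on-call psychiatrist as back-up. Patients also hold the contact information: "Insurance information and all contact details are provided in the informed consent document".

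The Procedure section gives the follow-up visits: "At three and 6 months, a more extensive evaluation will be performed". Table 1 dates them from ECT completion.

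Between visits, Assessment of depression relapse describes a text message every two weeks: "The text messages will be sent using SurveySignal at 18.00 h containing a link to a two question LimeSurvey questionnaire". The wording of both questions is printed, and both concern core depressive symptoms. A yes to either, or no reply within 24 hours, leads to a telephone call. The only content described for that call is the depressive episode module of the MINI.

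The Procedure section also makes one laboratory finding reportable without reference to the visit question: "If renal function deteriorates during follow-up this should be reported as an adverse event and may necessitate lithium discontinuation".

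**The concern.** The trial's active search for adverse events runs on a slower clock than its other contact with patients. It reaches everyone about every two weeks to look for relapse, yet it asks about health problems only when they attend. An open question answered from memory over two to three months tends to lose minor events and to misplace the dates of others. That matters more than usual here: the Background section reports lasting subjective memory loss after ECT in a sizeable share of patients, and the trial measures such complaints with the SSMQ.

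For serious events, the 24-hour rule says how fast a known event must be passed on. It is not in itself a means of finding the event. Take a patient admitted for a medical reason who answers the text and says no to both mood items. No trial contact described for the period before the next visit would reveal that admission unless the patient or the treating physician came forward.

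At stake are the completeness and dating of the adverse-event record in the months after training.

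**Working it through.** The plan gives no figure for the recall interval, so there is none to reproduce. The check is calendar arithmetic on the visit schedule, with one month taken as 30.44 days (365.25 / 12).

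**Inputs**
- Start of training: 0 to 7 days after ECT (Intervention group and Control group; the maximum is 7 days).
- Length of training: 12 to 14 days. Participant retention and withdrawal allows 14 days. The 12-day minimum is my assumption for five sessions a week over two weeks.
- Post-training assessment: 1 to 7 days after completion (Table 1).
- Later visits: 3 and 6 months after ECT completion (Table 1).
- Survey interval: 2 weeks (Assessment of depression relapse).

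**Day of the post-training assessment, counted from ECT completion**
- Earliest: 0 + 12 + 1 = day 13.
- Latest: 7 + 14 + 7 = day 28.

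**Recall windows**
- Three months: 3 × 30.44 = 91.3 days.
- Post-training to month 3, shortest: (91.3 − 28) / 7 = 9.0 weeks.
- Post-training to month 3, longest: (91.3 − 13) / 7 = 11.2 weeks.
- Month 3 to month 6: 91.3 / 7 = 13.0 weeks.

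**Against the existing contact rhythm**
- First window: 9.0 / 2 = 4.5 and 11.2 / 2 = 5.6, so 4 to 5 full fortnights.
- Second window: 13.0 / 2 = 6.5, so 6 full fortnights.
- The recall period is thus about 4.5 to 6.5 times the two-week interval at which the trial already contacts patients.

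**Which events would surface between visits, on the text as written**

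| Situation | Described route to the trial |
|---|---|
| Patient does not answer the text within 24 h | Telephone call |
| Patient answers yes to a mood item | Telephone call |
| Patient or treating physician reports the event | Emergency route or 24-hour rule |
| Renal function deteriorates | To be reported as an adverse event (Procedure) |
| Patient answers no to both mood items and nobody reports | None until the next visit |

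The last row is the gap. It applies to any non-serious event that the patient does not volunteer, and to a serious event that neither patient nor physician reports.

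**The case against.** The strongest reply is that this is an article condensing a fuller protocol, and that its safety section already holds the essentials: a non-leading question, a 24-hour rule, an emergency route with a back-up, and contact details for patients. Who reports a serious event between visits, when the 24 hours start, and how laboratory results reach the trial are details such an article may leave out. I accept that and make no finding of them. It does not answer the narrower point, because the visit question and the content of the fortnightly survey are both stated, the latter item by item.

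The term control visit is not defined, so equating it with the 3- and 6-month visits is an inference. It is a reasonable one, since no other in-person follow-up visits are described.

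Several stronger readings are tempting, but the document does not support them.
- A reader might infer that the visit question is the only way events are collected. The 24-hour rule, the emergency route and the separate duty to report renal deterioration are further routes.
- A reader might infer that renal events are collected only every three months. The treating physician tests monthly, and the Procedure section makes deterioration reportable without tying it to a visit.
- A reader might infer that the trial cannot support any safety statement about the training. Training takes place in the clinical center over two weeks with daily researcher contact, and an assessment follows within 1 to 7 days. The long windows come after exposure has ended.
- A reader might infer that unnoticed lithium changes undermine the relapse analysis. No stated analysis conditions on lithium status, so learning of a change later would not alter the planned chi-square or log-rank test.

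**Conclusion.** The point holds in a limited form. Active adverse-event questioning is described only at control visits. If these are the 3- and 6-month visits, patients are asked to recall about 9 to 11 weeks and then 13 weeks, although a two-week contact already exists and could carry the question. The likely result is that some non-serious events are missed or misdated, and that detection of a serious event between visits depends on a report or on a call triggered for another reason. The document gives no event rate, so the number of events affected cannot be estimated.

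The conclusion rests on three things: my reading of control visit, the dating of visits from ECT completion, and the assumed 12-day minimum for training. The last affects only the upper end of the first window. The matter concerns data capture and is worth changing because the change is cheap. It does not touch the sample size, the primary outcomes or the planned tests.

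**What to change.** Add one yes/no item to the fortnightly survey and to the script of the follow-up call: whether the patient has had any new health problem or hospital admission since the last message. A researcher follows up each yes and records what happened and when. The existing 24-hour route to the principal investigator then applies only to events that meet the definition of serious, so that minor complaints do not enter it. Keep the open question at the visits, and say in the Adverse events section which visits count as control visits.

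The cost is one survey item, one line in the call script, and some additional calls for minor complaints. No new contact is needed, and no visit, treatment or clinical rule changes.

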### Assessment

#### Depression related measures

##### HAM-D

The Dutch version of the HAM-D will be used to provide an objective measure of depressive symptoms and severity of depression. The HAM-D is a clinician rated questionnaire with 17 items scored on a three or five-point Likert-type scale. The questionnaire includes items concerning general symptoms of depression, as well as items specifically focused on mood, insomnia, and suicidal ideations [39, 40].

##### BDI-II

The Dutch version of the BDI-II will be used to measure depression severity, to monitor clinical response, remission, and possible relapse. The BDI-II is a 21-item self-report questionnaire with good validity and reliability; the internal consistency was described as around 0.9 and the retest reliability ranged from 0.73 to 0.96 [41, 42].

##### RDQ

Moreover, the Remission from Depression Questionnaire (RDQ) will inform about seven domains: symptoms of depression, non-depressive symptoms, features of positive mental health, coping ability, functioning, life satisfaction, and a general sense of well-being. The RDQ is a 41-item questionnaire showing good validity and allowing a broader perspective conform a biopsychosocial approach instead of focusing only on depressive symptoms [43, 44].

The HAM-D, BDI-II and RDQ will be completed at inclusion, after completion of the ECT course, after the intervention (active placebo or CCT) and at 3 and 6 months post-ECT (Fig. 1).

#### Rumination

##### RRS

The 10-item Dutch version of the Ruminative Response Scale (RRS-10) will be used to monitor rumination or repetitive negative thinking as this is a well-established cognitive risk factor for MDE. This self-report scale has demonstrated to be a reliable and valid instrument [45].

#### Quality of life

##### QLDS

To assess impact of ECT and cognitive control training on the perceived quality of life and emotional wellbeing, the Dutch version of the QLDS [46, 47] will be used. This 34-item questionnaire, developed by qualitative interviews, asks patients to rate statements regarding fulfillment of human needs such as ‘I take good care of myself’ and ‘I like to know what is going on in the world’. The QLDS, which has demonstrated good reliability and internal consistency, will be completed at inclusion, after completion of the ECT course, after the intervention (active placebo or CCT), and at 3 and 6 months post-ECT (Fig. 1).

#### Cognitive functioning

##### CANTAB

In order to assess the patients’ cognitive functioning, three tests of the Cambridge Neuropsychological Test Automated Battery (CANTAB®) were selected to cover (working) memory and executive functioning: Pattern Recognition Memory (measuring visual pattern recognition memory) and One Touch Stockings of Cambridge (measuring spatial spanning and working memory). A third test, Motor Screening was included to measure general sensorimotor skills. CANTAB® tests will be measured before ECT, after ECT, and after CCT completion (Fig.1).

##### PASAT

A non-adaptive version of the PASAT task will be used to assess task-specific cognitive transfer following (as compared to before) CCT [25, 48]. In line with the adaptive PASAT, patients are confronted with a continuous stream of digits and have to respond to the last two heard digits. Following a practice phase consisting of 10 trials, participants will complete a test phase which consists of three blocks of 60 trials each. Task difficulty increases over the different blocks, using an ITI of 4000, 2000, and 1500 ms for the first, second, and third block respectively.

##### SSMQ

To assess subjective cognitive functioning the Dutch version of the Squire Subjective Memory Questionnaire (SSMQ) will be administered at inclusion, after completion of the ECT course, after the intervention (active placebo or CCT) and at 3 and 6 months post-ECT (Fig.1). This 18-item self-report questionnaire uses a Likert scale to assess various aspects of subjective memory. The SSMQ is the most widely used scale for measuring subjective memory post-ECT [49].

##### Qualitative interviews

Qualitative interviews will be conducted to assess subjective memory complaints, acceptability of the cognitive remediation task and satisfaction of patients and family members (e.g., spouse). Interviews will be conducted after completion of CCT or placebo training.

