### Hypotheses

On our primary outcome measure, depressive symptomatology as measured by HAM-D, BDI-II and RDQ, we expect a reduction in patients that received 2 weeks of CCT as compared to the active placebo condition following ECT. On our secondary outcome measures we expect [1] reduced cognitive complaints (SSMQ), [2] improved cognitive functioning (CANTAB, PASAT), [3] reduced rumination (RRS-10, 4) enhanced quality of life (QLDS) in patients that received the cognitive control training compared to active placebo. These effects are expected immediately after the CCT as well as within the 6 months follow up period. Beneficial effects will also be reflected in reduced risk for relapse of depression during the period of 6 months follow-up. Moreover, we expect more positive treatment evaluations by both patients and their peers, increased patient satisfaction and acceptability of ECT in patients that received CCT as compared to an active placebo condition following clinical response ECT.

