### Study design and setting

This study uses a single blind mixed methods randomized controlled superiority trial with an embedded qualitative component. Participants will be recruited from one study site in a rural ECT-clinic in Belgium. Eligible participants will be encouraged to participate through flyers and posters in the ECT-clinic. Referring physicians will be informed of the study protocol. Participants will give informed consent for the study, cognitive control training or placebo post-ECT, prior to the start of electroconvulsive treatment.

The study has one intervention arm (cognitive control training) and one active placebo arm. All patients who give consent for participation and who fulfil the inclusion criteria will be randomized. Upon registration in the computer-based training by the allocated researcher, the computer will randomly allocate participants to either cognitive control training or placebo condition (e.a., computerized full random number generator). The researcher will monitor adherence to placebo or cognitive control training. Outcome assessors or ECT-physicians will only be involved in recruitment, ECT and post-intervention follow-up. They will not be involved during the two-week intervention phase of the study. Thus, randomization will be conducted without any influence of the principal investigators or outcome raters and both outcome assessors, ECT-physicians and participants will be blinded. Study data will be collected using digital and paper forms. Only outcome assessors and researchers will have access to the data. Data will be stored on a secure, password-controlled, server hosted at Ghent University. Qualitative interviews will be conducted in both arms after completion of CCT or placebo training. This study is in accordance with the Declaration of Helsinki (2013) and approved by the Ethical Committee of the Ghent University Hospital.

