Primary outcome(s)	Change in severity of depressive symptoms, clinician-rated (HAM-D) Change in severity of depressive symptoms, self-reported (BDI-II) Change in depressive symptoms and quality of life, self-reported (RDQ) Time Frame:1–7 days before first ECT session, 1–7 days post ECT completion, 1–7 days after intervention/placebo completion, 3 months after ECT completion, and 6 months after ECT completion
Key secondary outcomes	Subjective memory complaints (SSMQ) Time Frame:1–7 days before first ECT session, 1–7 days post ECT completion, 1–7 days after intervention/placebo completion, 3 months after ECT completion, and 6 months after ECT completion Quality of Life in Depression Scale (QLDS) Time Frame:1–7 days before first ECT session, 1–7 days post ECT completion, 1–7 days after intervention/placebo completion, 3 months after ECT completion, and 6 months after ECT completion Rumination (RRS-10) Time Frame:1–7 days before first ECT session, 1–7 days post ECT completion, 1–7 days after intervention/placebo completion, 3 months after ECT completion, and 6 months after ECT completion Cognition (CANTAB) Time Frame:1–7 days before first ECT session, 1–7 days post ECT completion, 1–7 days after intervention/placebo completion, 3 months after ECT completion, and 6 months after ECT completion Cognition (Paced Auditory Serial Addition Task - PASAT) Time Frame:1–7 days before first ECT session, 1–7 days post ECT completion, 1–7 days after intervention/placebo completion, 3 months after ECT completion and 6 months after ECT completion Acceptability and satisfaction: Qualitative interviews Time Frame: 1–30 days after CCT training completion Time to relapse Time Frame:Up to 6 months monitoring Facial features from video footage Time Frame:2 weeks during CCT or placebo intervention

**Table 2 Tab2:** Summary of protocol amendments

Protocol version	
1. December 2017	Original
2. August 2018	Qualitative interviews added
3. December 2019	Overall changes to protocol - Changes in outcome parameters (SSMQ, RDQ) - Changes to aPASAT training - Inclusion of facial videotaping - Extension of study duration

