#### Intervention group

Patients in the intervention group will start the CCT training after completion of ECT with a maximum time interval of 7 days. They will perform ten sessions of the adaptive PASAT (aPASAT) on a computer in the clinical center, completing five sessions per week (400 trials per session) for a period of 2 weeks using Inquisit 5 (Millisecond, 2016). During the adaptive PASAT, participants are confronted with a continuous stream of digits (auditory; 1–9), during which they continuously need to respond to the sum of the last two heard digits. The task starts using an inter-trial interval (ITI) of 4000 ms. Every four consecutive correct responses, the ITI decreases with 100 ms, reflecting an increase in task difficulty. Vice versa, following four consecutive incorrect responses, task difficulty decreases as shown by an increase in ITI of 100 ms. Throughout the CCT task, facial video footage will be collected. Patients who complete at least 6 CCT sessions will be regarded as CCT-completers. Patients who fail to complete more than half of the CCT sessions will be excluded. To date there is no data indicating the minimum amount of completed aPASAT training sessions for optimal results.

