#### Participant retention and withdrawal

Once a participant is randomized, investigators will make every reasonable effort to follow the patient for the entire 6-month follow-up period. During the cognitive control training patients will be motivated daily by researchers to complete their training. Participants have 14 days to complete 10 training sessions. The rate of loss-to-follow-up is estimated at 5 to 10% after completion of ECT treatment. Systematic methods and reminders for contacting patients, scheduling appointments, and monitoring retention will be developed by the study site.

Participants may withdraw consent for study participation for any reason at any time. For participant safety reasons, investigators may also withdraw participants from the study at any time. In case of non-adherence or non-retention, a final outcome assessment will be planned, if possible, collecting following data; SSMQ, BDI-II, HAMD, RDQ, RRS-10, QLDS and reasons for non-adherence or non-retention.

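### Acceptability interviews are timed from completion of training, and patients who stop early have no scheduled interview, so the findings risk favouring those who tolerated the task

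*Protocol article*

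**What the plan says.** The protocol article fixes the timing of the interviews in three places, each time by completion of training.

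- Qualitative interviews (under Assessment): "Interviews will be conducted after completion of CCT or placebo training".
- Study design and setting: "Qualitative interviews will be conducted in both arms after completion of CCT or placebo training".
- Table 1, key secondary outcomes: "Acceptability and satisfaction: Qualitative interviews Time Frame: 1–30 days after CCT training completion".

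Their purpose is given under Qualitative interviews: "Qualitative interviews will be conducted to assess subjective memory complaints, acceptability of the cognitive remediation task and satisfaction of patients and family members". They serve the third aim of the trial, the patients' evaluation of adding the training to ECT.

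Two sentences under Intervention group separate completers from others: "Patients who complete at least 6 CCT sessions will be regarded as CCT-completers" and "Patients who fail to complete more than half of the CCT sessions will be excluded".

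Participant retention and withdrawal describes what happens otherwise: "In case of non-adherence or non-retention, a final outcome assessment will be planned, if possible, collecting following data". The list that follows has six scales (SSMQ, BDI-II, HAM-D, RDQ, RRS-10, QLDS) and the reasons for non-adherence or non-retention. The interview is not on it.

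Under Hypotheses, the investigators expect more positive treatment evaluations, and "increased patient satisfaction and acceptability of ECT in patients that received CCT as compared to an active placebo condition".

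**The concern.** A patient who gives up the training because it is too hard or too frustrating provides direct evidence on whether the task is acceptable. If the interview is offered only to those who completed training, the sample is selected on something close to the quality being studied. Accounts of why the task was hard to bear would be under-represented, and the overall picture would probably be too favourable.

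The protocol itself treats tolerance of the task as a live issue. Researchers are to motivate patients daily to finish, and the video footage is to be examined for frustration and engagement.

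The comparison between arms is a second matter. The adaptive task asks for running sums at a pace that follows performance, whereas the control task asks only for the most recent digit. If more patients stop in one arm than in the other, the interviewed groups are selected differently, and a contrast in satisfaction or treatment evaluation would partly reflect that.

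**Working it through.** **1. Who has a scheduled interview?** Ten sessions are planned.

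| Sessions attended (CCT arm) | Status under Intervention group | Interview scheduled? |
|---|---|---|
| 10 | completer | yes |
| 6 to 9 | completer (at least 6) | yes, if completion is read through this definition |
| 5 or fewer | not more than half of 10; excluded | no provision found |

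The two sentences under Intervention group agree with each other: more than half of 10 means at least 6. The gap is therefore mainly at five or fewer sessions. That section does not say what such patients are excluded from. The threshold is worded for CCT sessions, and the Control group section states none.

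**2. Is there another route to an interview?** The final assessment for non-adherent or non-retained patients is the only candidate. It names six scales and the reasons for stopping, and it is planned only if possible. The scales thus have a stated route for early stoppers, and the interview has none.

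**3. Is there a figure in the plan to check?** There is none for the interviews. The only related number is the sample size. For a chi-square test with 1 degree of freedom, w = 0.3, α = .05 and power .80, N = (1.960 + 0.842)² / 0.3² = 7.85 / 0.09 = 87.2, rounded up to 88, which reproduces the stated N. It does not depend on the interviews.

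**4. How large could the effect be?** Let d be the share of randomised patients not interviewed, A_c the acceptability among those interviewed and A_d the acceptability among those not interviewed. The overstatement is A_c − [(1 − d)A_c + dA_d] = d(A_c − A_d).

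The protocol gives none of these three quantities. For illustration only, take A_c = 80% (assumed). For d, borrow 5% and 10% from the loss-to-follow-up estimate under Participant retention and withdrawal, which is not a rate of stopping training, and add 20% as a wider assumption.

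| A_d (assumed) | d = 5% | d = 10% | d = 20% |
|---|---|---|---|
| 0% | 4 points | 8 points | 16 points |
| 20% | 3 | 6 | 12 |
| 50% | 1.5 | 3 | 6 |
| 80% | 0 | 0 | 0 |

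For example, 0.10 × (80 − 20) = 6 points.

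Recruitment continues until 88 patients have completed the training, so those who stop come on top of the 88. At d = 5% about 88/0.95 ≈ 93 are randomised and about 5 not interviewed; at d = 10%, about 88/0.90 ≈ 98 and about 10. These counts are for both arms together.

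The table shows direction and range only. The interviews are to be analysed by qualitative methods, so no acceptability percentage will be estimated.

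**The case against.** The strongest reply is that completion is simply the label of a visit. Table 1 times the depression, memory, rumination and quality-of-life scales after completion of the intervention or placebo as well, yet the main analyses are by intention to treat, and every randomised patient is to be followed for six months where reasonably possible. On that reading the interview falls after the two-week phase, whoever finished it. This has force: a reader might infer that early stoppers are never interviewed, and no sentence says so. But the separate definition of completers and the exclusion of the rest weaken this reading, and for early stoppers the scales have a stated fallback that the interview lacks.

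Other stronger readings also fail.

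- A reader might infer that nothing is learned from those who stop. Their reasons are to be recorded if possible. That is less than an interview, but it captures part of the information.
- A reader might infer that acceptability is overstated by some definite amount. No stopping rate is given and no acceptability rate is given or planned, and the bias is zero if stoppers do not differ.
- A reader might infer a stated hypothesis that the task is more acceptable in one arm. The hypothesis names acceptability of ECT, a different construct; treatment evaluations and satisfaction are the parts that this point touches.
- A reader might infer that the adaptive task only gets faster. It also slows after four consecutive errors, so greater stopping in that arm is possible but not established.

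Finally, the sampling frame and mode of interview are details that an article commonly leaves to the full protocol, and their absence is not criticised here. The point rests on what the article does state: the timing, the exclusion and the content of the final assessment.

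**Conclusion.** The point holds in a limited form. Followed as written, the plan schedules no interview for patients who stop with about five or fewer sessions, so findings on acceptability of the task and on satisfaction risk favouring those who tolerated it. The likely direction is favourable, on the assumption that those who stop find the task less acceptable than those who continue. Contrasts between arms in treatment evaluation and satisfaction could also be affected, but only if stopping differs by arm, on which the protocol gives no information. The size cannot be derived from the document. Severity is minor: one qualitative secondary outcome serving the third aim, with no effect on the primary analysis or the sample size.

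**What to change.** 1. In Study design and setting, Qualitative interviews and Table 1, time the interview 1 to 30 days after the last training session attended, in either arm and whether or not training was completed.
2. Add the interview to the final assessment under Participant retention and withdrawal.
3. Under Intervention group, state that exclusion for too few sessions does not apply to the interview. Without this, the amended timing would conflict with that section.
4. Report the number of non-completers interviewed, and their reasons for stopping, beside the interview themes.

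The cost is a few more interviews by the existing team and a change of wording in the registered time frame. Some patients who stop will decline, so the selection would be reduced rather than removed. The change is best made prospectively, because experiences not collected near the time of stopping are hard to recover later.
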